### Recruitment

Participants will be recruited from among patients visiting our outpatient clinic, so no other efforts to recruit potential subjects are required. Patients will receive a detailed explanation of the risks and benefits of the trial to ensure that they fully understand the specifics of the study, and then they will be asked to voluntarily provide a signed informed consent form.

## Assignment of interventions: allocation

### Sequence generation

All patients will be randomized to one of the following four groups at a 1:1:1:1 ratio one day prior to surgery: P0 (*n* = 33), P25 (*n* = 33), P50 (*n* = 33), and P75 (*n* = 33) groups. The assignment will be conducted by computer-generated random sequence with block randomization, stratified by sex and age (< 65 and ≥ 65 years). Based on the potential risk of age and gender having an impact on the pain relief and side effect outcomes after surgery, as suggested by previous literature, we performed stratification accordingly [19]. To maintain an equal allocation of participants to each of the four treatment groups, we will use a block size of 4 (one allocation for each treatment group within a block). The generated sequence will be masked from the primary investigators and will be recorded in the randomization list.

### Concealment mechanism

The allocation sequence will be concealed using sealed, opaque, and stapled envelopes and will not be opened by the investigators involved in the management or assessment of the study participants. After the allocation, trial participants, care providers, and outcome assessors will remain blinded throughout the trial. The placebo will have the same appearance, route of administration, and dosing schedule as those of the study drug to maintain participant blinding. Neither the names of the study drugs nor the study arm will be included in the medication packs.

### Implementation

The allocation sequence will be generated by a member of the study staff not involved in the care of the participants, outcome assessment, or analysis of the unblinded data. The unblinded staff member in charge of the allocation will deliver the concealed sequence to the pharmacy department of our institute, where the unblinded pharmacist will provide the participants with their allocated study drug based on the randomized sequence. The unblinded staff and pharmacist are not involved in the management or assessment of the study participants.

## Assignment of interventions: blinding

### Who will be blinded

The participants and investigators will remain blinded to the group allocation until the trial has ended.

### Procedure for unblinding if needed

Emergency unblinding of the patient allocation will be performed if patients meet the following criteria: severe violation of the treatment plan; severe adverse reaction to the study drug, including drowsiness, dizziness, and peripheral oedema; request by the patient or their family members to stop the trial; perioperative complications, including infection, vascular injury, hematoma, and prosthesis-related complications; and death during the trial.

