### Criteria for discontinuing or modifying allocated interventions

Participants who present with severe drowsiness, dizziness, visual disturbance, or swelling that precludes the use of pregabalin will discontinue the trial and stop taking their allocated treatment. Participants who develop infection, nerve injury, hematoma, or metal-related complications following surgery or those who request discontinuation will also be excluded from the trial.

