### Adverse event reporting and harms

During the intervention, the principal investigator will actively seek and be informed of any occurring adverse events. All adverse events will be recorded in the CRF. The principal investigator will report any serious adverse events to the institutional review board within 15 days of notice. Adverse events that are not serious will be reported every 3 months. When reporting adverse events or harm, the causality, timing of occurrence, severity, seriousness, and provided management will be reported together.

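### Unblinding is mandatory for a plan violation, a request to stop and surgical complications, with no need-to-know condition, which conflicts with the unqualified promise of blinding and exposes the harm judgements

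*Protocol article*

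**What the plan says.** All references are to the protocol article.

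- The section *Procedure for unblinding if needed* opens its list of triggers this way: "Emergency unblinding of the patient allocation will be performed if patients meet the following criteria: severe violation of the treatment plan". A wish to leave is also on the list ("request by the patient or their family members to stop the trial"), and so is a serious drug reaction ("severe adverse reaction to the study drug, including drowsiness, dizziness, and peripheral oedema"). Complications around surgery and death complete it.
- *Who will be blinded* states: "The participants and investigators will remain blinded to the group allocation until the trial has ended".
- *Concealment mechanism* states: "After the allocation, trial participants, care providers, and outcome assessors will remain blinded throughout the trial". Neither blinding statement carries an exception.
- The section *Criteria for discontinuing or modifying allocated interventions* deals with drug reactions as follows: "Participants who present with severe drowsiness, dizziness, visual disturbance, or swelling that precludes the use of pregabalin will discontinue the trial". Surgical complications and a request to discontinue also end participation.
- *Adverse event reporting and harms*: the principal investigator reports serious events within 15 days and other events every 3 months, and "the causality, timing of occurrence, severity, seriousness, and provided management will be reported together".
- *Sequence generation*: "we will use a block size of 4 (one allocation for each treatment group within a block"), within strata of sex and age group.

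**The concern.** An emergency code-break normally exists so that a patient can be treated with knowledge of the allocation. Here the code opens because an event is on a list. At least two of those events, a severe plan violation and a request to stop, call for no knowledge of the arm in themselves. Perioperative complications open it with no stated link to a need to know. Followed literally, the rule makes unblinding an ordinary consequence of leaving the trial.

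Two things are at stake.

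- **Harms.** Safety is part of the objective, and the background section describes sedation, dizziness and peripheral oedema as dose-dependent. Someone who knows whether a patient had placebo or the highest dose may rate causality or severity differently.
- **Allocation.** With one patient per arm in every block of four, each opened code rules out an arm for patients who enter that block later.

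**Working it through.** **Step 1. Triggers beside the reasons for leaving.** The left item comes from the discontinuation section, the right item from the unblinding section.

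- Severe drowsiness, dizziness, visual disturbance or swelling | severe adverse reaction (open list naming drowsiness, dizziness, oedema)
- Infection | infection
- Hematoma | hematoma
- Metal-related complication | prosthesis-related complication
- Nerve injury | not named, but the list of complications is open
- Request to discontinue | request to stop
- Not listed | severe plan violation, vascular injury, death

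Nearly every reason for leaving is therefore also a reason to open the code. *Eligibility criteria* adds a third list, which excludes patients with any postoperative complication, and with death among its examples.

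**Step 2. How many codes.** The plan's own total reproduces: 28 / (1 − 0.15) = 32.9, rounded up to 33 per group, and 33 × 4 = 132. The expected loss is 15% under *Sample size* and 20% in the section on non-adherence and missing data.

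- 132 × 0.15 = 19.8
- 132 × 0.20 = 26.4
- If only half of the 20% meet a trigger: 132 × 0.10 = 13.2

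**Step 3. What an opened code reveals about later patients.** Let q be the share unblinded, independent between patients. The patient in position k of a block has k − 1 predecessors. If x of their codes are open and known, the chance of guessing this patient's arm is 1/(4 − x). So

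g(k) = Σ over x of C(k−1, x) q^x (1−q)^(k−1−x) / (4 − x), averaged over k = 1 to 4.

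For q = 0.20:

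- g(1) = 0.250
- g(2) = 0.8/4 + 0.2/3 = 0.267
- g(3) = 0.64/4 + 0.32/3 + 0.04/2 = 0.287
- g(4) = 0.512/4 + 0.384/3 + 0.096/2 + 0.008 = 0.312
- Average = 1.115/4 = 0.279

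| q | g(1) | g(2) | g(3) | g(4) | Average | Fourth patient certain (q³) |
|---|---|---|---|---|---|---|
| 0.10 | 0.250 | 0.258 | 0.268 | 0.278 | 0.263 | 0.001 |
| 0.15 | 0.250 | 0.263 | 0.277 | 0.294 | 0.271 | 0.003 |
| 0.20 | 0.250 | 0.267 | 0.287 | 0.312 | 0.279 | 0.008 |

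**Step 4. Why only earlier codes count.** Recruitment is expected from October 2022 to 31 May 2024, about 20 months. With strata assumed equal, 132 / 20 / 4 = 1.65 patients per stratum per month, so a block takes about 4 / 1.65 = 2.4 months to fill. Treatment and assessment last 72 h, so members of one block are rarely in the trial together. The exposure falls on patients not yet entered.

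**Step 5. Harm judgements.** No arithmetic applies. A severe drug reaction opens the code, the report with causality and severity may follow up to 15 days or 3 months later, and no section requires those judgements to be fixed before the code is opened.

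**The case against.** The best defence is that the blinding sections give the general rule and the unblinding section, which follows directly, gives the exception. That is right as far as it goes: having an emergency procedure does not contradict a double-blind design. What stands is that the exception is too broad and automatic, and that neither general statement acknowledges it.

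There are also stronger readings that a reader might infer and that the article does not support.

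- **That severe visual disturbance and nerve injury end participation but leave the code closed.** Both lists of unblinding triggers are open, so these events may be covered. The differing lists need reconciling but are not proof of error.
- **That the same investigators recruit, manage and grade harms.** The article says that the principal investigator reports causality and severity, and that research associates complete the case report forms. It does not say who judges. For a severe drug reaction, some view of severity and cause must also exist before the trigger is met.
- **That most blocks are compromised.** At q = 0.20, 1 − 0.8⁴ = 59% of blocks would hold an opened code. That assumes that every expected withdrawal is unblinded, and it counts blocks where the opened code belongs to the last patient.
- **That the efficacy comparison is seriously biased.** Patients who leave give no further data, and the analysis is restricted to those who complete, so unblinded patients largely drop out of it.

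The envelopes are also kept from investigators who manage or assess participants, and the sequence is masked from the primary investigators. Who receives a broken code is not stated, and an article may leave that to the full protocol. The leak is therefore a risk, not an established fact.

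**Conclusion.** The point holds as a fault of wording with a real consequence. The text as written opens the code for events that are not emergencies in themselves, makes unblinding a likely accompaniment of withdrawal, and does not fit the unqualified blinding statements.

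- **Harm attribution** is the main risk. Its size cannot be computed from the article, because it depends on who learns the code and when the judgement is recorded.
- **Allocation of later patients** is a secondary and modest risk. The average chance of guessing the arm rises from 25% to about 26% (10% unblinded), 27% (15%) or 28% (20%, the upper case). Certainty about a fourth patient arises in under 1% of blocks.

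These figures assume independent unblinding, complete blocks, and a person guessing who knows both the opened codes and the block boundaries. They also assume that only patients who leave are unblinded; anyone unblinded for a plan violation who stayed in the trial would come on top.

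**What to change.** - State that a plan violation or a request to stop does not by itself open the code.
- Reconcile *Eligibility criteria*, *Criteria for discontinuing or modifying allocated interventions*, *Concealment mechanism*, *Who will be blinded* and *Procedure for unblinding if needed* on which clinical events do open it. That choice belongs to the investigators.
- Handle any code-break through the pharmacist, who is already unblinded, and disclose the allocation only to those who need it. Assessors and other investigators stay blinded.
- Record causality and severity, as judged at that moment, before the code is opened.
- Optionally vary the block size, which makes block boundaries harder to infer.

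This is a change of protocol wording. It needs no extra patients. The cost is a short request form for the pharmacist.

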## Data collection and management

### Plans for assessment and collection of outcomes

Data will be collected using case report forms (CRFs) on paper, which will be completed by trained CRAs from days 1 to 4. The schedule of assessments is shown in Table 2.

**Table 2 Tab2:** Schedule of patient enrolment, interventions, and assessments

**Time point**	Study period							
	Enrolment	Allocation	Post-allocation					
	D-14	D0	Surgery	1 h	6 h	24 h	48 h	72 h
**Enrolment:**	X							
Eligibility screen	X							
Informed consent	X							
Inclusion and exclusion criteria	X							
Allocation		X						
**Interventions:**								
Pregabalin				X	X	X	X	X
Placebo				X	X	X	X	X
**Assessments:**								
VAS score				X	X	X	X	X
IV PCA usage				X	X	X	X	X
Frequency of rescue analgesic use				X	X	X	X	X
Frequency of nausea and vomiting				X	X	X	X	X
Sedation				X	X	X	X	X
Dizziness				X	X	X	X	X
Headache				X	X	X	X	X
Visual disturbance				X	X	X	X	X
Swelling				X	X	X	X	X

### Plans to promote participant retention and complete follow-up

The intervention will occur during the first 72 h after surgery and will be monitored closely by the study team throughout that period. Evaluation of postoperative pain using the VAS and postoperative complications are part of the routine postoperative patient examination. Patients do not need to adhere to any other specific tasks, and there is no outpatient clinic follow-up as part of the study, so there will be no difficulties in completing the evaluation.

### Data management

Data for screening will be recorded by the CRAs. After enrolment, all study data will be recorded into the CRFs on paper. Medical history will be obtained by interviewing the participants. Data will be entered into a computer for analysis by [name] and [name]. Data will be stored for 3 years after the end of the study. Data accuracy will be checked by the principal investigator of the study.

### Confidentiality

Patients will be referred to exclusively by their participant numbers. Clinical information, informed consent, and CRFs will be stored separately within a double locker until expiration of the storage period, after which the data will be destroyed.

### Plans for collection, laboratory evaluation, and storage of biological specimens for genetic or molecular analysis in this trial/future use

This trial does not involve collection of biological specimens.

## Statistical methods

### Statistical methods for primary and secondary outcomes

The primary objective of this study is to compare the effect of different doses of pregabalin to placebo on pain relief and the need for additional analgesics during the 72-h period following surgery, at various time points. Additionally, the study aims to assess the incidence of adverse events during this period. Primary outcomes include the VAS pain score, total dose of IV PCA administered, and frequency of rescue analgesic administered. We will use the Kolmogorov–Smirnov test (K-S test) to assess the normality of the primary outcome measure. If the normality assumption is met, we will perform an analysis of variance (ANOVA) analysis; otherwise, we will use the Kruskal–Wallis test for comparison. We will use the Bonferroni’s method for conducting subgroup analysis to account for multiple comparisons. Categorical variables, such as the incidence and frequency of nausea and vomiting caused by IV PCA or the incidence of side effects (sedation, dizziness, headache, visual disturbance, and swelling), will be compared between the groups using the chi-squared test. Statistical analyses will be performed using SPSS 20.0 (IBM, Armonk, NY, USA). In all analyses, *P* < 0.05 will be taken to indicate statistical significance.

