### Outcomes

We will examine the efficacy of pregabalin on postoperative pain using the variables described in the literature [12]. The primary outcomes are pain intensity measured on a visual analogue scale (VAS) (length, mm), total administered amount of IV PCA measured (volume, mL), and frequency of rescue analgesics administered (the number of administrations, according to the type of rescue analgesic, and the total amount of morphine equivalent dose). The VAS score is evaluated using a pain ruler marked from 0 (no pain) to 100 (maximal pain) mm, with patients directly indicating their pain level. The secondary variables are the incidence and frequency of nausea and vomiting caused by IV PCA. Assessments of all variables will be performed during the first 72 h following the arrival of the participant at the general ward, subdivided into four periods: 1–6 h, 6–24 h, 24–48 h, and 48–72 h. We will evaluate pain between the midpoint and the end of each of the four time zones, aiming to measure as close to the end time as possible and use the pain scores at all four time points as the primary outcome. The pain levels in each time zone will be compared to see if they differ depending on the treatment method. Through this, we will ascertain how the treatment effect changes over time and how these changes differ among different treatment groups. Through these variables, we plan to check the effects of pregabalin on reduction of postoperative pain and IV PCA usage. In addition, we will examine whether reduction of IV PCA usage has a beneficial effect on the patient by reducing the incidences of common side effects, nausea and vomiting.

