### Sample size

The prior calculation of the sample size indicated that at least 28 subjects were required for each group. For calculation, the software G*Power 3.1.9.7 was used with a statistical power of 0.95 at an effect size of 0.448 with an alpha level of 0.0167. The effect size was determined based on a previous study [18]. In this study, three groups—those treated with placebo, pregabalin 75 mg, and pregabalin 150 mg—each comprised 28 participants. The groups were compared based on their PCA usage, with mean values of 95.3, 96.6, and 105.2 respectively, and an approximate standard deviation of 10. For the purposes of this study, which involves four instead of three groups, a fourth hypothetical group was considered with the mean value of 96.6, which is the median value of the three established groups. Based on this data, Cohen’s *f* was calculated, resulting in an effect size of 0.448. To compare the four groups through Bonferroni’s test, the alpha level was set at 0.05 divided by 4, which is 0.0167. When calculated based on these parameters, the total sample size needed is found to be 112, and the number of participants needed per group is 28. Considering a follow-up loss of approximately 15%, 33 participants per group would be required, resulting in a total of 132 participants needed for the study.

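### Three primary outcomes over four periods are all read at P < 0.05, with no control across outcomes or periods and no rule for which result makes the trial positive

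*Protocol article*

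**What the plan says.** Three variables share primary status. In the statistical methods section: "Primary outcomes include the VAS pain score, total dose of IV PCA administered, and frequency of rescue analgesic administered". The Outcomes section and the Abstract list the same three.

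Each is assessed repeatedly. The Outcomes section has all variables collected over 72 h, "subdivided into four periods: 1–6 h, 6–24 h, 24–48 h, and 48–72 h", and the Abstract attaches the same split to the primary outcome. For pain the plan is explicit that it will "use the pain scores at all four time points as the primary outcome", and adds: "The pain levels in each time zone will be compared to see if they differ depending on the treatment method". The rescue outcome is broken down further, as "the number of administrations, according to the type of rescue analgesic, and the total amount of morphine equivalent dose".

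Each comparison is a four-group ANOVA or Kruskal–Wallis test. The threshold is general: "In all analyses, *P* < 0.05 will be taken to indicate statistical significance". The only multiplicity step is a Bonferroni correction for what the article calls subgroup analysis. The section on additional analyses plans none, so this most naturally means comparisons between arms.

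The Sample size section works with a different level, "with an alpha level of 0.0167", which it links to a Bonferroni comparison of the groups.

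**The concern.** The trial is described as a superiority trial, yet it names no key outcome, key time point, testing order or requirement that all outcomes succeed. Followed as written, the plan produces a dozen or more primary P values, each read at 0.05. One isolated significant period on one outcome could then be reported as a positive primary result. The closing sentence of the Discussion already anticipates evidence of efficacy down to the lowest dose, so what counts as such evidence needs to be fixed in advance.

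This is not a detail left to a later analysis plan. The article itself fixes 0.05 for every analysis and makes all four pain time points primary. A later document could control the error only by departing from those statements.

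**Working it through.** **1. The plan's own sample size.** Inputs from the Sample size section: four groups, f = 0.448, alpha 0.0167, power 0.95. For a one-way ANOVA with noncentrality f² × N, the smallest balanced N with at least 95% power is 112 (28 per group, power 95.5%). Allowing 15% loss, 28/0.85 = 32.9, so 33 per group. The stated figures reproduce. The test that was sized is therefore the four-group omnibus F test at 0.0167.

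**2. Number of primary tests.**
- Plain reading: 3 outcomes × 4 periods = 12.
- Lenient reading, with only VAS tested by period and PCA and rescue use as 72-h totals: 4 + 1 + 1 = 6.
- Most lenient, one test per outcome: 3.
- Rescue use split into the three named drugs plus morphine equivalents, each by period: 4 + 4 + 4 × 4 = 24.

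**3. Familywise error at 0.05 per test.** If the tests are independent and any one significant result counts, it is 1 − 0.95^k:

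| k | Calculation | Error |
|---|---|---|
| 3 | 1 − 0.8574 | 14.3% |
| 6 | 1 − 0.7351 | 26.5% |
| 12 | 1 − 0.5404 | 46.0% |
| 24 | 1 − 0.2920 | 70.8% |

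**4. Allowing for correlation.** The document gives no correlations, so these are assumptions. Twelve null ANOVAs were simulated with 4 arms × 28, normal data and 20,000 runs per setting:

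| Between periods | Between outcomes | Error, 12 tests |
|---|---|---|
| 0.3 | 0.5 | 40% |
| 0.5 | 0.5 | 37% |
| 0.7 | 0.5 | 31% |
| 0.7 | 0.7 | 28% |
| 0.8 | 0.7 | 24% |
| 0.9 | 0.7 | 20% |

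For 6 tests with a common correlation of 0.9 the error is 11%; for 3 tests at 0.9 it is 9%. Every reading and every setting tried exceeds 5%.

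**5. What 0.0167 would and would not do.**
- Applied to all 12 tests, independent: 1 − 0.9833^12 = 18.3%. Over the correlation grid (10,000 runs per setting) it is about 9–18%.
- Applied to three tests, one per outcome: 1 − 0.9833³ = 4.9%.
- Bonferroni over all 12: 0.05/12 = 0.00417 per test. With f = 0.448 and 112 evaluable, power falls from 95.5% to 88.6%.

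**6. Where 0.0167 comes from.** The Sample size section gives it as 0.05 divided by 4, but 0.05/4 = 0.0125. The value 0.0167 is 0.05/3.

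**The case against.** Four points can fairly be made in the plan's defence.

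- **A reader might infer that 0.0167 is never used in the analysis.** The document does not support that. A between-arm Bonferroni step is planned, and for three dose-versus-placebo comparisons it amounts to 0.05/3 = 0.0167 each. Adjusted P values read against 0.05 are the same thing. What stands is narrower: the omnibus test was sized at 0.0167 and will be read at 0.05. The between-arm step, on its likeliest reading, does not reach across outcomes or periods.
- **The percentages could be taken as properties of the trial.** They are not. The 46% is exact only for 12 independent tests, and the lower values depend on assumed correlations, so none of them is a floor. Period-by-period comparison is spelled out only for pain, so 12 is the plain reading and not a certainty.
- **A reader might infer that the plan lets any one significant test establish efficacy.** It does not say so. It does not exclude it either, and that gap is the difficulty.
- **A reader might infer that no controlled superiority conclusion is possible.** That goes too far. A rule fixed before unblinding repairs the problem with the same data, and even Bonferroni over all 12 tests keeps 88.6% power at the stated effect size.

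None of this supplies the missing control across outcomes and periods.

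**Conclusion.** The concern holds. The article makes three outcomes primary over four periods, reads every test at 0.05, and gives neither error control across them nor a success rule. If any one significant primary test may count, the familywise error is 46% for 12 independent tests and about 20–40% under moderate to strong assumed correlations. Independent tests on the more lenient counts of 6 and 3 give 26.5% and 14.3%. These figures rest on the number of tests, on the any-one-counts rule that the plan leaves open, and on correlations the document does not report. Separately, and without any such assumption, the alpha for the four-group test differs between the Sample size section (0.0167) and the statistical methods section (0.05).

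**What to change.** Amend the protocol and registry wording before unblinding, in one of two ways.

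1. **Keep three primary outcomes.** Define one confirmatory 72-h test for each of VAS, IV PCA amount and rescue use, choosing a single rescue measure. Read each four-group test at 0.05/3 = 0.0167. Familywise error over the three tests is then about 4.9%, and the level matches the sizing.
2. **Name one primary outcome.** Use total 72-h IV PCA use, since PCA usage is the variable the trial was sized on. Test VAS and then rescue use in fixed sequence, stopping confirmatory claims at the first non-significant result.

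In either case:
- Keep Bonferroni for between-arm comparisons, within the alpha given to that outcome. For three dose-versus-placebo comparisons this is 0.0167/3 = 0.0056 each under option 1 and 0.05/3 = 0.0167 each under option 2. State which comparisons are meant and drop the term subgroup analysis.
- Report the four periods as estimates with confidence intervals and no confirmatory claim.
- State the same alpha, with its correct derivation, in the Sample size and statistical methods sections.
- Restate power for the test chosen. The stated N was derived for an omnibus test on PCA usage, so it says nothing directly about pairwise comparisons, VAS or rescue use. At the stated f = 0.448 with 112 evaluable, omnibus power is 95.5% at 0.0167 and 98.4% at 0.05. The means and SD listed in the Sample size section give f = 0.395 (root mean squared deviation 3.95, divided by 10), for which power at 0.0167 is 87.7%, so the effect size should be rechecked at the same time.

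The change needs wording only and no new data. Its cost is that fewer results can be called confirmatory.

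### A Kolmogorov–Smirnov pre-test chooses between ANOVA and Kruskal–Wallis, so the same primary outcome can be judged on means in one period and on ranks in the next

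*Protocol article*

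**What the plan says.** The protocol article, under Statistical methods for primary and secondary outcomes, sets out a two-stage rule: "We will use the Kolmogorov–Smirnov test (K-S test) to assess the normality of the primary outcome measure", followed by "If the normality assumption is met, we will perform an analysis of variance (ANOVA) analysis; otherwise, we will use the Kruskal–Wallis test for comparison". The same paragraph lists three primary outcomes: "Primary outcomes include the VAS pain score, total dose of IV PCA administered, and frequency of rescue analgesic administered".

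Under Outcomes, all variables are "subdivided into four periods: 1–6 h, 6–24 h, 24–48 h, and 48–72 h". For pain, the plan is to "use the pain scores at all four time points as the primary outcome", and "The pain levels in each time zone will be compared to see if they differ depending on the treatment method". The stated purpose is that "we will ascertain how the treatment effect changes over time and how these changes differ among different treatment groups".

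Under Sample size, the trial is sized from group means of PCA usage and a common standard deviation, converted to Cohen's f. That is a comparison of means.

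The article does not say whether the normality test is run per arm, pooled or on residuals, which critical value it uses, or what follows if it passes in one period and fails in another.

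**The concern.** ANOVA compares means, in mm or mL. Kruskal–Wallis compares ranks and yields no difference in those units. If the pre-test passes for VAS in two periods and fails in the other two, the four results do not lie on one scale and cannot be read as a course over time, which is what the Outcomes section asks for. The analysis may also leave the mean-based footing on which the trial was sized. Which of these happens depends partly on sampling noise in the normality test.

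At stake is how interpretable the primary results are, and how firmly the primary analysis is fixed before the data are seen.

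**Working it through.** **Inputs from the protocol article.** Three primary outcomes and four periods; 28 per group, 112 in total; f = 0.448, alpha 0.0167, power 0.95; 15% loss; means 95.3, 96.6, 105.2 and a hypothetical 96.6, with SD about 10; analysis level 0.05.

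**Assumptions (the article gives no outcome distributions).** Moderate right skew is represented by gamma distributions of shape 8 and 4, with skewness 2/√8 = 0.71 and 2/√4 = 1.0. Kolmogorov–Smirnov is run at 5%, pooled over 112 patients unless stated. Where periods are correlated, the correlation is 0.5.

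**1. The plan's own figure.** One-way ANOVA with noncentrality N·f² = 112 × 0.448² = 22.5 and 3 and 108 degrees of freedom, at alpha 0.0167, gives power 0.955. N = 112 is reproduced. Then 28/0.85 = 32.9, so 33 per group and 132 in total. This calculation covers the ANOVA branch only.

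**2. How often the pre-test rejects normality.** The 5% critical value of D at n = 112 is about 0.084 when mean and SD are estimated from the data, and about 0.127 when they are treated as known. Independent simulation runs gave:

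| Distribution | Estimated-parameter value | Uncorrected value |
|---|---|---|
| Gamma, shape 8 | 45–48% | 2–3% |
| Gamma, shape 4 | 74–79% | 9–13% |

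**3. Chance that the four periods do not all get the same test.** With rejection probability p and independent periods this is 1 − p⁴ − (1 − p)⁴.

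- p = 0.45: 1 − 0.041 − 0.092 = 0.87
- p = 0.79: 1 − 0.390 − 0.002 = 0.61
- p = 0.02: 1 − 0.000 − 0.922 = 0.08
- p = 0.13: 1 − 0.000 − 0.573 = 0.43

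Periods within a patient are correlated. At correlation 0.5, with the estimated-parameter value, mixing was 84% (shape 8) and 68% (shape 4; 72% when run on residuals). The unit of testing also matters. The next figures use the estimated-parameter value; the first is for pooled residuals, the second for testing each arm and counting any rejection:

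- exactly normal data: 18% and 56%
- VAS in 1 mm steps with falling means: 37% and 60%
- VAS rounded to 5 mm: 69% and 88%

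**4. Rescue counts.** For Poisson counts with mean 1, normality was rejected in every sample, so mixing was 0%. The switching problem concerns VAS and PCA volume.

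**5. Error rates and verdicts.** The type I error of the two-stage rule was 0.048 to 0.053 at nominal 0.05. Under moderate skew the power of the two tests differed by only a few percentage points. At the 0.05 level, ANOVA and Kruskal–Wallis gave opposite verdicts in 2–4% of data sets with no effect or with the Sample size means at SD 10, and in about 10–12% when those differences were halved.

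**The case against.** The strongest reply is that the rule is written in advance with both branches named, is common practice, and does no measurable damage to type I error and little to power. All of that stands. A reader might infer that the two-stage procedure is invalid or inflates false positives; the calculations do not support that.

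A second reply is that the article does not say the pre-test is applied separately by outcome and period, since it speaks of the outcome measure in the singular. It also does not say that raw outcomes rather than residuals are tested. Both are fair. Application by outcome and period is an inference, though a natural one: three outcomes in four periods have separate distributions, and the groups are compared in each period. It would be going too far to state as fact that the test is run on the raw outcome. How the check is executed may be set out in a fuller document. The switching rule itself, however, is stated here, so it is not an omission left to that document.

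Third, the percentages rest on assumed distributions. It is tempting to call the pre-test a coin toss, but only shape 8 with the estimated-parameter value comes near 50%. Likewise, disagreement of about 10% applies to intermediate effects and not in general.

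Finally, the lack of a dose-minus-placebo estimate is not peculiar to Kruskal–Wallis: an omnibus ANOVA F-test gives none either, and the article does not bar reporting one. That is a reporting matter and not part of the fault.

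**Conclusion.** The point holds in a limited form. The rule lets the data choose the test, and with it the effect scale, for the primary outcomes. That sits badly with the aim of following the effect across four periods and with a sample size built on means. For VAS and PCA volume, mixed tests across periods are likely if the estimated-parameter critical value is used (about 61–87% under moderate skew) and less likely with the uncorrected one (about 8–43%). These ranges depend on the assumed skew, the correlation between periods and application by period.

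The consequence is loss of comparability and of a firmly fixed analysis. It is not an invalid test, an inflated error rate or a material loss of power. It should be treated as a cheap improvement.

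**What to change.** Delete the Kolmogorov–Smirnov step and name one analysis per outcome, used in every period.

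- **VAS and PCA volume:** the linear (ANOVA) model on means with heteroscedasticity-robust standard errors, reporting each dose-minus-placebo difference with its confidence interval. Separate models per period would still not test change over time. A repeated-measures version with a treatment-by-period term would address that aim directly.
- **Number of rescue administrations:** a count model, such as negative binomial, with rate ratios and confidence intervals.
- **Morphine-equivalent dose of rescue:** this is an amount and not a count, so the count model does not cover it. Name one separate method in advance.
- **Kruskal–Wallis:** keep as a pre-stated sensitivity analysis.

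The cost is about a paragraph of analysis wording, settled before unblinding. No new data are needed, and the planned 112 (132 with dropout) keeps its ANOVA basis. The downside is some loss of power against the rank test under very strong skew; the sensitivity analysis would show whether this matters.
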